## Abstract

**Background:** Exercise is an essential pillar for human health, as it contributes to physical, mental, and emotional well-being. Well-recognized international organizations, such as the World Health Organization, advocate for integrating exercise into healthy lifestyles, recognizing its importance in disease prevention and improving quality of life. However, despite the consensus on its value, there is no universal agreement on specific prescriptions for vulnerable groups, highlighting the need for personalized approaches that consider the unique characteristics and needs of everyone. Emerging studies have demonstrated that exercise training performed at the intensity that elicits maximal fat oxidation improves insulin sensitivity, cardiorespiratory fitness, and body composition in patients with obesity, making it a highly effective strategy for long-term weight management and metabolic health in this specific population. **Methods:** The present study protocol settles the basis for a 16-week randomized clinical trial based on exercise prescription at the maximal fat oxidation rate combined with resistance training in young individuals with overweight and obesity. **Expected Results:** This study will elucidate how FatMax, with or without resistance exercises, can enhance metabolic flexibility, increase fat oxidation, and improve body composition, evaluating changes in biochemical parameters (cholesterol, glucose, triglycerides, and inflammatory markers), metabolic biomarkers (determination of fat and carbohydrate utilization rates during rest and exercise), and epigenetic indicators (focusing on microRNAs associated with adipogenesis, inflammation, and fat metabolism). ClinicalTrials.gov identification number: NCT06553482 (FatMax Training on Metabolic and Epigenetic Parameters).

## 1. Introduction

Obesity is a major public health challenge affecting millions of people in Mexico and around the world. This noncommunicable disease has been dramatically increased in recent decades, being recognized as one of the major risk factors for chronic diseases such as diabetes, cardiovascular disease, and certain types of cancer. By 2022, it was estimated that 890 million adults suffered from obesity [1], and the trend continues to increase independent of age, sex, and socioeconomic status.

The critical levels of this disease urgently demand the need to address this health crisis on multiple fronts. Traditional strategies to combat obesity have focused primarily on individual responsibility, emphasizing the need to improve dietary habits and increase physical activity [2]. However, reducing obesity to a mere willpower issue is insufficient to understand the complexity of the problem, which involves genetic/epigenetic, psychological, social, economic, environmental, and individual factors. Concerning lifestyle moderators, dietary counseling and exercise prescription have a profound impact on energy metabolism and body weight regulation in this population. Furthermore, distinct genetic polymorphisms and microRNA molecules have also been associated with obesity and the particular response to diet and exercise [3,4].

The current guidelines provided by the American College of Sports Medicine and the World Health Organization for obesity management emphasize that weekly energy expenditure stimulated by exercise should be higher than 2000 kcal/week to create a negative energy balance that induces body weight reduction. However, emerging research indicates that maximizing fat oxidation during exercise, rather than solely focusing on overall energy expenditure, may offer a more effective approach for the prevention and management of obesity [5]. In fact, exercise training performed at the intensity of maximal fat oxidation (FatMax) enhances metabolic flexibility and fat utilization during exercise, improving cardiovascular health in patients with obesity [6]. Additionally, FatMax training alleviates insulin resistance and systemic inflammation, decreases visceral adiposity, and improves lipid metabolism, making it a highly effective strategy for long-term weight management and metabolic health in this population [7]. FatMax training stands apart from other exercise modalities, such as HIIT and MICT, for its capacity to optimize fat oxidation as the primary energy source, which may result in greater fat loss. Furthermore, its moderate intensity makes it safer and more sustainable for overweight or obese populations, improving adherence and minimizing injury risk. In contrast, while HIIT is effective in enhancing cardiovascular fitness and reducing exercise duration, it may not be well tolerated by sedentary individuals or those with metabolic disorders [8].

It should be noticed that 8 to 20 weeks of FatMax training seem to not alter free fat mass or muscle mass in this population [7,9]. Therefore, combining FatMax training with resistance exercises may increase the lean mass of subjects with obesity, preventing sarcopenic obesity and cardiometabolic disorders related to low muscle mass over the long term [9,10]. On the other hand, it has been demonstrated that fat oxidation during exercise is determined by age, sex, body fat levels, genotype, and the type of exercise in individuals with obesity [11,12]. However, the influence of these moderators on the cardio-metabolic adaptations stimulated by FatMax training remains understudied. In addition, there is scarce information about the molecular mechanisms that become activated by FatMax training to induce positive adaptations in metabolic function and overall fitness. To be precise, Bogdanis et al. [13] and Tan et al. [14] reported that skeletal muscle mitochondrial respiratory capacity and the activity of lipoprotein lipase increased significantly after 10 weeks of FatMax training in overweight and obese individuals. Nevertheless, the impact of FatMax training on epigenetic biomarkers related to mitochondrial biogenesis and the regulation of fatty acid metabolism, such as microRNAs, remains unexplored. In this context, microRNAs such as miR-1, which regulates the expression of CPT1, a key enzyme in the transport of fatty acids to the mitochondria, and miR-145, miR-20a-5p, and miR-29a, which modulate the activity of CD36, a protein involved in the uptake of long-chain fatty acids, have been linked to the development of obesity due to their role in lipid metabolism regulation. However, exploring how these microRNAs can be modified by physical exercise interventions, such as those performed at the intensity of maximal fat oxidation (FatMax), is essential to better understand the underlying molecular mechanisms that could optimize both the prevention and treatment of obesity, thereby enhancing intervention strategies to promote overall well-being [11].

We hypothesize that FatMax training, with or without resistance exercises, will significantly improve body composition (reduce body fat and increase muscle mass) and metabolic flexibility, increase fat oxidation, and alter epigenetic markers related to adipogenesis and inflammation in overweight and obese young adults. Looking to examine which biological and lifestyle factors moderate the adaptations to FatMax training, we will investigate the influence of age, sex, body fat levels, genotype, diet, psychological variables, and the type of exercise.

## 2. Experimental Design

### 2.1. Type of Study

This research is a randomized controlled clinical trial designed to evaluate the impact of exercise training at maximal fat oxidation intensity (FatMax) combined with resistance training on metabolic, biochemical, and epigenetic parameters in young adults with overweight and obesity. The trial is set to last 16 weeks, and its design adheres to the SPIRIT standards and CONSORT guidelines to ensure rigor and replicability in the reporting process.

### 2.2. Participants Eligibility Criteria

The study will recruit 156 sedentary young adults aged between 18 and 35 years, all of whom will have a body mass index (BMI) ≥ 25 kg/m^2^. Participants will be recruited through snowball sampling. The participants will be eligible to participate in this study if they meet the eligibility criteria detailed in Table 1.

### 2.3. Interventions or Treatments

Participants will be randomly assigned to one of three groups: Group A: Will perform low-intensity training within the FatMax zone. Group B: Will perform FatMax training combined with resistance exercises. Group C (Placebo Group): The placebo group will undergo a ‘masking training’ that does not involve significant physiological or metabolic changes. This training will consist of stretching sessions with smooth, controlled movements that do not significantly impact metabolism or induce relevant physiological changes, while maintaining the perception of physical activity and an isoenergetic diet.

### 2.4. Dependent Variables

The dependent variables include body composition (fat mass and muscle mass), biochemical parameters (glucose, cholesterol), metabolic markers (fat and carbohydrate oxidation rates), and epigenetic markers (microRNAs associated with adipogenesis and fat metabolism).

### 2.5. Groups and Randomization

Randomization of participants will be conducted using SPSS 22 statistical software to ensure balanced distribution between gender and BMI categories (overweight and class 1 obesity). Participants will be randomly assigned to the three study groups, and the allocation will be coded to maintain group balance.

### 2.6. Duration and Timeline

This study will last for a total of 16 weeks, with assessments conducted at the beginning of this study (baseline) and after the 16-week intervention period to measure the changes in body composition, metabolic parameters, and epigenetic markers.

### 2.7. Control Procedures

To control potential confounding variables, participants in the control group will follow an isoenergetic diet, and dietary intake will be monitored regularly throughout this study. Individuals with less than 75% attendance at the training sessions will be excluded from the final analysis. To address potential non-compliance or dropout in this exercise intervention, a plan will be implemented that includes weekly check-ins, flexible scheduling, and the provision of motivational incentives. Close monitoring will be conducted to detect early non-compliance, with personalized support provided as needed. In cases of dropout, exit interviews will be conducted to identify barriers and improve future retention strategies. This approach aims to maximize adherence and minimize dropout throughout this study. Other variables, such as sleep quality and psychological status, will be monitored to ensure consistency across all groups.

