## 4. Detailed Procedure

### 4.1. Sample Size Calculation

To carry out the present study, 156 young sedentary adults with overweight/obesity will be recruited through a snowball sampling. Considering the body composition changes as the primary outcome, the minimum sample size calculated for the present protocol was 44 participants to reliably detect an effect size of δ ≥ 0.5, assuming a two-sided criterion for detection that allows a maximum Type I error rate of α = 0.05 with a probability of 0.9, and considering a 20% dropout of participants, the sample size has been fixed to 52 participants per group. The statistical software used to determine the sample size was G*Power (v3.1.9.7, Universität Kiel, Düsseldorf, Germany) [15]. 

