#### 4.5.4. Dietary and Psychological Counseling

For internal control, covariates that could influence the findings (uncontrollable variables) will be monitored, including dietary patterns, mental health, and adherence of the individuals during the trial period. The food intake of all participants will be monitored through a 24 h quantitative recall of typical days (typical days before the start and at the end of the intervention), as well as a food frequency questionnaire. Food scales will be used to increase precision in food portions. Diet records will be analyzed for total calories, protein, carbohydrate, and fat intake (Diet Analysis Plus, ESHA Research, Salem, OR, USA). Dietary control will be complemented with biomarkers of nutrient intake such as urinary nitrogen and blood concentrations of cholesterol, triglycerides, and glucose.

The psychological status of the individuals will be evaluated using the validated instrument “Depression, Anxiety, and Stress Scale-21” (DASS-21), complemented by sleep-wake patterns obtained through a sleep diary and sleep quality assessment questionnaires (Pittsburgh Sleep Quality Index and Insomnia Severity Index).

Only individuals who complete at least 80% of all training sessions and measurements outlined in this intervention will be included in the data to ensure adherence to the treatments and the validity of the findings. Additionally, electronic and personal contact via text messaging will always be enabled for study follow-up.

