#### 4.5.5. Data Analysis

The normality and homoscedasticity of the variables will be assessed using the Kolmogorov–Smirnov and Levene tests for each group. A student’s *t*-test will be used to analyze the differences between the pre- and post-treatment values for each variable if the data follows a normal distribution. If the data are non-parametric, the Mann–Whitney U test will be used. Statistical analysis between treatments will be conducted using ANOVA with Tukey’s post-hoc test in the case of parametric distribution and/or Kruskal–Wallis H and Dunn’s Post-hoc test for non-parametric distribution, with a Bonferroni setting for comparing intervention-induced changes. Additionally, Pearson and/or Spearman correlation tests will be used to establish associations between variables. Multivariate linear regression models will also be constructed to explore the contribution of treatment on main outcomes, which will be adjusted by potential confounder factors including age, sex, dietary variables, psychological variables, and baseline measurements. Moreover, multiple imputations will be used for generating replacement values for missing data. Statistical significance will be considered at *p* < 0.05, and all statistical analyses will be conducted using IBM SPSS package version 22 (SPSS Inc., IBM Company, Chicago, IL, USA) and GraphPad Prism v8.1 (GraphPad Software, La Jolla, CA, USA).

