## Figures and Tables

**Figure 1 jfmk-09-00214-f001:**
[figure not shown]
Randomized clinical trial design. EFM: FatMax training; EFM + MRE = FatMax plus low resistance muscle training. Note: All participants will follow an isoenergetic diet, and those individuals who attend less than 75% of the training sessions will be excluded from the analysis.

**Table 1 jfmk-09-00214-t001:** Eligibility criteria to participate in the clinical trial.

Inclusion Criteria	Exclusion/Elimination Criteria
Both genders	≥100 mL of alcohol consumption per week
18–35 years old	Consume a dietary supplement or pharmacological treatment
Energy expenditure < 600 METs a week	Have limitations to perform regular physical activity
Body mass index ≥ 25 kg/m^2^	Have a chronic non-communicable disease
Acceptance of informed consent	Answer “yes” to any of the questions on the Physical Activity Readiness-Questionnaire for Everyone (PAR-Q+), which represents a health risk.
	<80% attendance at exercise sessions

METs: Metabolic Equivalents of the task.

**Table 2 jfmk-09-00214-t002:** Exercise protocols for the assessment of metabolic function and cardiorespiratory conditioning.

	Treadmill	Cycle Ergometer
Warm up	Duration: 5 min Intensity: 3 km/h; 0% inclination	Duration: 5 min; 40 Watts; 60 RPM
Phase 1	Duration of stages: 3 min Initial load: 3 km/h; 1% inclination Progression of the load: 1 km/h Conclusion: RER = 1.0 for 30 s	Duration of stages: 3 min Initial load: 40 Watts; 60 RPM Progression of load: 20 Watts Conclusion: RER = 1.0 for 30 s
Phase 2	Duration of stages: 1 min Load progression: 1 km/h Conclusion: (i) Rate of perceived exertion = 10; (ii) Heart rate ≥ 90% MHR	Duration of stages: 1 min Load progression: 20 Watts Conclusion: (i) Rate of perceived exertion = 10 Effort = 10; (ii) Heart rate ≥ 90% MHR

MHR: theoretical maximum heart rate; RER: respiratory exchange rate; RPM: revolutions per minute.

**Table 3 jfmk-09-00214-t003:** FatMax and Resistance Training characteristics.

Training	Frequency	Intensity	Time	Type
FatMax	Fout times a week	Individualized according to the Heart Rate at thetMax	Sessions between 1–1.5 h	Aerobic exercise
Resistance Training	Two times a week	Individualized, with a total of 3 sets of 8–12 reps per muscle group a week	Sessions between 40–60 min	Resistance training (weight lifting)

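### Randomised participants are dropped from the final analysis for low attendance, under two conflicting cut-offs (75% and 80%), and no all-randomised analysis is stated

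*Protocol article*

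**What the plan says.** The protocol article gives the attendance rule in four places:

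- Section 2.7: "Individuals with less than 75% attendance at the training sessions will be excluded from the final analysis".
- Figure 1 note: "those individuals who attend less than 75% of the training sessions will be excluded from the analysis".
- Section 4.5.4: "Only individuals who complete at least 80% of all training sessions and measurements outlined in this intervention will be included in the data".
- Table 1, in the column for exclusion and elimination: "<80% attendance at exercise sessions".

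Allocation is random. Section 2.5 says "Participants will be randomly assigned to the three study groups, and the allocation will be coded to maintain group balance". The arms are then compared directly. Section 4.5.5 says "Statistical analysis between treatments will be conducted using ANOVA with Tukey’s post-hoc test in the case of parametric distribution", with a rank-based alternative and a covariate-adjusted regression. For incomplete data the same section says "multiple imputations will be used for generating replacement values for missing data", without saying for which participants. Nowhere does the article state an analysis of all randomised participants in their assigned arms.

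**The concern.** Whether someone attends 75% or 80% of sessions becomes known only after randomisation, and may depend on the assigned programme and on how the participant is doing. Comparing only those above a threshold compares self-selected subsets, so the balance that randomisation provides is no longer guaranteed. The adjusted regression in Section 4.5.5 controls for measured covariates and cannot restore it.

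The demands also differ by arm. Table 3 gives four FatMax sessions a week, and group B has two resistance sessions on top. Group C has stretching sessions in Section 2.3, but in Section 4.2 it only maintains its activity. Selection may therefore be unequal, and the article does not make clear how the rule applies to C.

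Separately, two cut-offs define two analysis sets, and nothing says which governs. This affects every between-arm result, including the primary body-composition outcome.

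**Working it through.** **1. The rules side by side**

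| Place | Removed if | Further condition |
|---|---|---|
| Section 2.7 | under 75% of sessions | none |
| Figure 1 note | under 75% of sessions | none |
| Section 4.5.4 | under 80% of sessions | 80% of measurements as well |
| Table 1 | under 80% of sessions | none |

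Each cut-off appears twice, and the measurement condition once.

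**2. Who falls between the cut-offs**

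Inputs: 16 weeks (Section 2.6), and four FatMax and two resistance sessions a week (Table 3). Assumptions: these frequencies hold throughout, and B's two session types are counted together.

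- Group A: 16 × 4 = 64 sessions. 75% is 48; 80% is 51.2, so 52 are needed. Attending 48, 49, 50 or 51 is in under one rule and out under the other.
- Group B: 16 × 6 = 96 sessions. 75% is 72; 80% is 76.8, so 77 are needed. The gap is 72 to 76.

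The documents do not say how many people this would be. If attendance followed a beta distribution with mean 75–90% and SD 10–15% (assumed), about 2 to 10 of the 52 in an arm would change status with the cut-off.

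**3. Possible bias (illustration only)**

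The yardstick is the effect size in Section 4.1, where the minimum "was 44 participants to reliably detect an effect size of δ ≥ 0.5". That 44 is reproduced by a paired t-test at d = 0.5, two-sided α = 0.05 and 90% power (n = 43.995). Only δ = 0.5 is used below.

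Take a standard normal attendance propensity with correlation r to the standardised outcome change, and remove the lowest fraction p of an arm. The mean outcome of those retained shifts by r × φ(z_p)/(1 − p). The bias is the exercise-arm shift minus the control shift.

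- p = 0.05: 0.1031/0.95 = 0.109
- p = 0.20: 0.2800/0.80 = 0.350
- p = 0.30: 0.3477/0.70 = 0.497

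| Excluded, exercise vs control | r = 0.2 | r = 0.3 | r = 0.5 |
|---|---|---|---|
| 20% vs 5% | 0.048 | 0.072 | 0.121 |
| 20% vs 0% | 0.070 | 0.105 | 0.175 |
| 30% vs 5% | 0.078 | 0.116 | 0.194 |
| 30% vs 0% | 0.099 | 0.149 | 0.248 |

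The range is 0.048 to 0.248 SD. Divided by 0.5, that is about 10% to 50% of δ. With none removed from a control arm of 52 and 42 or 36 left in the exercise arm, the two-sided type I error of one such comparison would be about 6% to 21% instead of 5%. If p and r are the same in both arms, the two shifts cancel and the bias is zero.

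**4. Interaction with imputation**

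The main outcomes are assessed at baseline and after week 16 (Section 2.6). People who stop attending are those most likely to lack week-16 values, and the attendance rule removes many of them before imputation could be used.

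**The case against.** The strongest defence is that this is a condensed article and a separate analysis plan may define an all-randomised set. That would answer a mere omission. Here the article itself states the exclusion and states it inconsistently, so a plan that analysed everyone would contradict it.

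Other objections limit what can be claimed:

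- **Differential exclusion.** A reader might infer that the exercise arms must lose more people and that control stays nearly whole. The rule is a percentage and names no arm, and Section 2.3 gives control its own sessions, so control could lose as many. Unequal loss is plausible, not established.
- **Size under no true effect.** An observed attendance–outcome correlation would partly reflect training dose, which plays no part when there is no effect. Only its prognostic part biases a null comparison. The documents give no correlation and no arm-specific exclusion rate, only a 20% dropout allowance (Section 4.1).
- **Imputation.** It is tempting to say the rule makes imputation pointless. But measurements include items collected every four weeks (Sections 4.2 and 4.4) and many assays and questionnaires, so a retained participant may still have values to impute. Its use is narrowed, not removed.
- **Table 1.** The caption speaks of eligibility, which might suggest attendance is an entry criterion. The column also covers elimination, so it reads more naturally as removal after enrolment. The conflicting number remains.
- **Choosing the cut-off after seeing results.** The documents do not suggest any such intent, and the data analyst is to be blinded (Sections 4.2 and 5). The set is still not fixed in advance.

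**Conclusion.** The point stands as wrong in the text. Removal by post-randomisation attendance is the stated rule for the final analysis, the cut-off is contradictory, and no all-randomised analysis is stated. These conclusions need no assumption. The session counts in the gap rest on the Table 3 frequencies holding for 16 weeks and on pooling in B.

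The comparison may be biased, probably towards exercise, provided that better attenders would do better anyway and that more people are removed from the exercise arms. On the assumed inputs the bias is about 0.05–0.25 SD (10–50% of δ = 0.5), and near zero if selection is alike across arms. This illustrates what could be at stake; it does not estimate what will happen. The matter should be settled before any participant is eliminated, because week-16 data not collected from low attenders cannot be recovered.

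**What to change.** - Make the primary analysis all randomised participants in their assigned arm, whatever their attendance.
- Invite everyone, including low attenders and those who stop training, to the week-16 assessment, and apply the planned multiple imputation to values still missing.
- Reconcile Section 2.7, Section 4.5.4, Table 1 and the Figure 1 note to one attendance cut-off, used only to define a secondary per-protocol set. State whether the measurement condition belongs to that set and how sessions are counted in B.
- Reconcile Sections 2.3 and 4.2 on what group C does, so that it is clear how the per-protocol definition applies there.
- Describe the Table 1 entry as the definition of the per-protocol set, not as an exclusion or elimination criterion.

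**Cost.** Mostly wording. The estimated effect may be somewhat smaller than among adherers. The scheduled week-16 assessments must also be completed in people who might otherwise have been eliminated. If the 20% dropout allowance is a guide, that is about 0.20 × 156 = 31 people.

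### No week-16 assessment is provided for participants who stop training, and the adherence rules keep them out of both the analysis and the imputation, so the result describes adherent completers

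*Protocol article*

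**What the plan says.** - **Expected loss.** Section 4.1 takes body composition as the primary outcome and sets the group size with an allowance for loss: "considering a 20% dropout of participants, the sample size has been fixed to 52 participants per group".
- **Action on dropout.** Section 2.7: "In cases of dropout, exit interviews will be conducted to identify barriers and improve future retention strategies". No other step after dropout is stated, and stopping the training is not distinguished from leaving the study.
- **Outcome times.** Section 2.6: "assessments conducted at the beginning of this study (baseline) and after the 16-week intervention period". Section 4.5.1 plans two blood samples for each participant, on day 0 and day 112. Two items are more frequent: gas exchange during FatMax training (Section 4.4) and diet records in group C (Section 4.2), both every four weeks.
- **Who enters the data.** Section 4.5.4: "Only individuals who complete at least 80% of all training sessions and measurements outlined in this intervention will be included in the data". Section 2.7 and the note to Figure 1 exclude attendance below 75%. Table 1 lists attendance below 80% among the exclusion and elimination criteria.
- **Missing data.** Section 4.5.5: "multiple imputations will be used for generating replacement values for missing data". It does not say for which participants.

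**The concern.** Read together, these provisions work against each other. A participant who stops early is interviewed about barriers, is not provided with an endpoint measurement, and is then removed by the adherence rules. The imputation is left to work on people who kept training and were mostly measured.

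Stopping an exercise programme may well be related to how well it is tolerated and how well it works. The burden also differs by arm: Table 3 gives four FatMax sessions a week, and group B adds two resistance sessions, while group C is described as stretching (Section 2.3) or as maintaining its usual activity (Section 4.2). Different numbers and kinds of people may therefore drop out of each arm. A comparison restricted to adherent completers then loses the protection of randomisation and answers a narrower question than the effect of being assigned to A or B rather than C.

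An analysis plan can change who is analysed and how values are imputed, but it cannot supply endpoint values that were never collected. The return visit therefore has to be settled in the protocol and consent.

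**Working it through.** **1. The plan's own figures.** Section 4.1 states "calculated for the present protocol was 44 participants to reliably detect an effect size of δ ≥ 0.5"; its settings are two-sided α 0.05 and power 0.90. A two-sided paired t-test with standardised change 0.5 gives n = 44 (power 0.900). A two-sample t-test at the same settings needs 86 per group. So 44 reproduces as a within-group pre-post calculation, and the plan's 0.5 appears to be a pre-post effect. The 52 is close to 44 × 1.2 = 52.8; dividing by (1 − 0.2) would give 55. With 20% loss, 52 × 0.8 = 41.6 remain per group and 52 × 0.2 = 10.4 are lost. The design of the sample-size calculation is a separate matter; only the 20% and the 52 are needed here.

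**2. Who the adherence rules remove.** Take a participant with full attendance until stopping and a constant number of sessions per week over 16 weeks.
- 75% of sessions is reached at 0.75 × 16 = 12 weeks.
- 80% of sessions is reached at 0.80 × 16 = 12.8 weeks.

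Anyone who stops before week 12 fails both thresholds, whether or not they are measured at week 16. Someone who stops later may pass on sessions but can still fail on measurements: counting only the two scheduled assessments of body composition, blood and microRNA, a missed week 16 leaves 1 of 2, or 50%. The four-weekly items change that fraction somewhat, and the article does not say how measurements are counted.

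**3. What imputation would do if it reached them.** For outcomes seen only at baseline and week 16, with no off-training values, change within an arm can be learned only from those who stayed. A large simulation (2 million participants, two arms) used these assumptions: 20% dropout in each arm, completer effect 0.5 SD, no gain in dropouts, baseline-to-endpoint correlation 0.7, and regression on baseline fitted to completers within each arm.
- True effect in all randomised: 0.40 SD
- Imputed effect: 0.50 SD
- Completers only: 0.50 SD

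**4. Illustrative size.** With dropout fraction p and effect e in dropouts, the effect in all randomised is (1 − p) × 0.5 + p × e. Here 0.5 SD is an assumed between-arm effect in completers.

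| p | e (SD) | All randomised (SD) | 0.50 ÷ this |
|---|---|---|---|
| 10% | 0 | 0.45 | 1.11 |
| 10% | 0.25 | 0.475 | 1.05 |
| 20% | 0 | 0.40 | 1.25 |
| 20% | 0.25 | 0.45 | 1.11 |
| any | 0.5 | 0.50 | 1.00 |

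At 20% dropout the gap is 0.05-0.10 SD. The standard error of a two-arm contrast with 42 per arm is √(2/42) = 0.218 SD, so the gap is 0.23 to 0.46 of a standard error.

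**The case against.** **Silence is not refusal.** A reader might infer that dropouts go unmeasured. No section says so. The exit interview is the only stated action, but Section 2.6 sets the week-16 assessment without exception, Section 4.5.1 plans two blood samples for every participant, and a condensed article may omit follow-up detail. This stands: the supported statement is that such an assessment is not provided for. The stated adherence rules do not depend on that silence. They remove most people who stop, measured or not.

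**Imputation is not useless.** A reader might infer that no analysis could recover the effect. That goes too far. Multiple imputation is valid if outcomes are missing at random given the modelled variables, and reference-based or delta-adjusted imputation can represent stopping under stated assumptions. The imputation model may properly be left to an analysis plan. What the protocol does fix is that the people concerned are outside the data.

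**Not every outcome has only two time points.** Gas exchange every four weeks can give interim information on fat oxidation for A and B participants who stop later. This also stands, so the point is confined to body composition, blood and microRNA.

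**The size is assumed.** A reader might take an overstatement of 11-25% as established. It follows entirely from the assumed retained effect, and it treats 0.5 SD as a between-arm effect although the plan's figure fits a pre-post test. It shows scale only.

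**Conclusion.** The concern holds in limited form. As written, the between-arm result describes adherent completers, because the adherence rules remove most people who stop training and so keep the imputation from reaching them. The absence of any provision for a week-16 assessment means that relaxing those rules alone might leave little to analyse. Conversely, measuring people who stop would change little while the rules stand.

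The likely direction is overstatement of the benefit of A and B, but this rests on dropouts gaining less than completers, which the documents neither show nor exclude. Under the stated assumptions the gap is 0.05-0.10 SD at 20% dropout and 0.025-0.05 SD at 10%, and zero if dropouts gain as much as completers. It is below half a standard error, so it would not dominate the result, but it is avoidable and should be corrected.

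**What to change.** - **Section 2.7.** Separate stopping training from leaving the study. Invite everyone who stops training to the week-16 assessment already planned.
- **Sections 2.7 and 4.5.4, Table 1 and the note to Figure 1.** The session and measurement thresholds should no longer decide who enters the primary analysis. Analyse all randomised participants in their assigned group. Keep the adherent subset as a secondary analysis, with the 75% and 80% figures reconciled.
- **Section 4.5.5.** Apply the imputation to all randomised participants without a week-16 value, using whether they stopped training and any measured off-training values. Add a sensitivity analysis that does not assume that dropouts respond like completers.

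**Cost.** Protocol and consent wording, and return visits for about 10 participants per arm, using assessments already planned for all 156. Some will decline. The estimated effect will probably be smaller. In the illustration, two-arm power with all 52 per arm measured is 0.52-0.62 for an effect of 0.40-0.45 SD, against 0.62 for 42 completers per arm at 0.50 SD.
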